Ethiopia is an ideal setting for our proposed work, as it faces important tradeoffs between the benefits of milk production and consumption and AFM_1_ risk. Ethiopia has recently adopted a strict standard for AFM_1_ in milk, 0.5 µg/L (Ethiopian Standards Agency CES-278), which is often exceeded in raw milk samples from Ethiopia as shown by mean AFM_1_ levels ranging between 0.41 and 0.69 µg/L with a range of 0.028–4.96 µg/L.^14^ The action level for AFM_1_ in milk in the USA is the same, at 0.5 µg/L^15^; while the European Union standard is 0.05 µg/L.^16^ The recent lack of evidence linking AFM_1_ to cancer has led to the question of whether the standards set are reasonable.^12^ Moreover, dairy markets are important in Ethiopian livelihoods, particularly in rural areas where dairy is an important source of supplemental income.^17^ If excessively strict AFM_1_ standards are enforced in Ethiopian dairy markets, it could result in both economic losses from discarded milk, and nutritional losses due to negative public perception against milk consumption.^12 18^

To assess the relationship between AFM_1_ exposure and growth outcomes and the potential benefits and risks of AFM_1_ in milk in Ethiopia, we use a prospective longitudinal cohort design. Here, we describe the objectives, methods and expected outcomes of this study.

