## Objectives

Our goal is to determine whether AFM_1_ exposure through milk consumption is associated with child growth impairment over a period of 18 months in early childhood; then to compare this risk with the benefits of milk consumption. This evidence will inform policy recommendations for AFM_1_ regulation in dairy products in Ethiopia. The specific objectives of this study are to:

Determine the association between milk consumption and growth outcomes in children 6–36 months of age.Examine the association between AFM_1_ exposure and growth outcomes in children 6–36 months of age who consume milk.Compare the health benefits and risks associated with dairy consumption in relation to child growth outcomes.Develop policy recommendations for regulating AFM_1_ and communicating dairy benefits and risks.

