### Sample size calculations

Using the 2016 Ethiopia Demographic Health Survey^22^ and focusing on our primary anthropometric outcome variable, we have mean height-for-age z-scores (HAZ) in children under the age of 36 months of −1.46 (SD=1.56). With the significance level set at 5%, power at 80%, allowing for 10% attrition between survey rounds, and accounting for that not all children consume milk, the study requires approximately 1000 children to detect a 0.3 SD improvement in child HAZ. This minimum detectable effect size corresponds to the estimated association between household cow ownership and child HAZ (children starting at 6–18 months of age) in a study by Hoddinott *et al* in rural Ethiopia.^23^ Since we focus directly on children’s dairy consumption rather than cattle ownership, and our exposure variable is continuous rather than dichotomous, the expected magnitude of the association is likely to be larger than the association documented in Hoddinott *et al*.^23^ Thus, we expect this sample size to offer sufficient precision to detect positive and/or negative associations between AFM1 exposure and growth outcomes in this population.

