### Data analysis

#### Empirical approach

Descriptive analysis will focus on computing frequencies and percentages for categorical variables and summary statistics (like means, medians SD, IQR) for summarising continuous variables. To determine the association between dairy consumption and growth outcomes in children 6–18 months of age at the baseline, we will specify a least squares regression model as:

(1)
$$Y_{iv}=\alpha +\beta_{M}M_{iv}+X_{iv}^{\prime }\delta +\varepsilon_{iv}$$

where 
$Y_{iv}$
 is the anthropometric outcome for a child *i* residing in enumeration area *v* measured at various time points. Variable 
$M_{iv}$
 measures the child’s milk intake at various time points. The regression controls for child, parent and household characteristics that are captured in vector 
$X_{iv}$
. These control variables are observable characteristics that are likely to be correlated both with a child’s milk intake and his/her growth outcomes. The terms 
α
 and 
$\varepsilon_{iv}$
 in equation (1) represent the intercept and error term, respectively. The coefficient 
$\beta_{M}$
 quantifies the conditional association between a child’s milk intake and subsequent growth outcome, measured either as HAZ at the end line or as change in HAZ between the baseline and end-line surveys. Considering previous evidence from Ethiopia and elsewhere, we expect 
$\beta_{M}$
 >0.

To determine the association between AFM_1_ levels in milk and nutrient density in milk, we will conduct a univariate analysis on each of the macronutrients and micronutrients and then carryout bivariate tests with AFM_1_ levels in the same samples and determine if and how they are associated with each other.

To determine the association between AFM_1_ exposure and growth outcomes in children 6–36 months of age who consume dairy, we will test whether the consumption of AFM_1_-contaminated milk is associated with lower HAZ (ie, more growth faltering) controlling for confounders and co-factors, including the amount of milk consumed and nutrient content and pathogens in the milk. We will append equation (1) with a variable capturing the child’s AFM_1_ exposure (variable 
$A_{iv}$
). In this model, we also control for the estimated macronutrient and micronutrient content and pathogens (vector 
$C_{iv}^{`}$
) in the milk sample collected at the baseline from the household in which the child resides. We will also control for the child’s maize consumption (vector 
$H_{iv}^{`}$

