), since maize is also likely to be contaminated by aflatoxins in the Ethiopian setting.^34–37^ The estimated model can be defined as:

(2)
$$Y_{iv}=\alpha +\beta_{M}M_{iv}+\beta_{A}A_{iv}+\beta_{C}C_{iv}^{\prime }+X_{iv}^{\prime }\delta +H_{iv}^{\prime }\vartheta +\varepsilon_{iv}.$$

We expect that 
$\beta_{A}$
 < 0.

To compare the health benefits versus risks of dairy consumption in child growth outcomes, we will use the regression estimates from equation (2) to conduct joint hypothesis tests for 
$\beta_{M}$
 and 
$\beta_{A}$
, where the null hypothesis is that both of these coefficients are zero, to inform benefit-risk tradeoff of dairy consumption in the context of AFM_1_.

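### On its natural reading, the benefit-risk comparison takes the milk benefit from a model for milk consumers only, so the milk-versus-no-milk contrast does not enter it

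*Protocol article*

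**What the plan says.** All references are to the protocol article.

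- **Objectives.** The first objective relates milk consumption to growth, with no restriction to consumers. The second, on AFM1, concerns "growth outcomes in children 6–36 months of age who consume milk". The third is to "Compare the health benefits and risks associated with dairy consumption in relation to child growth outcomes".
- **Empirical approach, equation (1).** It addresses the "association between dairy consumption and growth outcomes in children 6–18 months of age at the baseline", again without restriction to consumers.
- **Empirical approach, equation (2).** It is introduced with the words "To determine the association between AFM_1_ exposure and growth outcomes in children 6–36 months of age who consume dairy". It adds AFM1 exposure (A), milk content and pathogens (C) and maize consumption (H) to equation (1).
- **Empirical approach, benefit versus risk.** For the third objective, "we will use the regression estimates from equation (2) to conduct joint hypothesis tests for" β_M and β_A, with the null that both are zero.
- **Sample size calculations.** About 1000 children are required, "accounting for that not all children consume milk". The share of consumers is not given.
- **Introduction.** One stated worry about strict AFM1 limits is "nutritional losses due to negative public perception against milk consumption".

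**The concern.** Restricting to consumers suits β_A, since a child who drinks no milk has no AFM1 exposure from milk. It suits β_M less well. Among consumers, β_M = 0 says only that drinking more rather than less is unrelated to HAZ. Whether drinking some milk is better than drinking none is part of the benefit of dairy consumption, and zero-intake children carry that information. Equation (1) uses them, but its estimate is not carried into the third objective.

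This comparison is meant to inform policy on AFM1 limits and on messages about milk. If much of the benefit comes from having any milk at all, the planned comparison could not see it, although the data would have been collected.

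**Working it through.** **1. Is there a stated figure that settles it?** No. The point turns on the analysis population, and the stated N of about 1000 cannot be checked without the consumer share. For two equal groups, two-sided 5%, 80% power, n per group = 2 × (1.96 + 0.84)² × SD² / δ²:

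- δ = 0.3 SD: 175 per group, 350 in total, 350 / 0.9 = 389 after 10% attrition.
- δ = 0.3 HAZ points, SD 1.56: 425 per group, 850 in total, 850 / 0.9 = 945 after attrition.

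Neither gives 1000 without an assumed share, so shares of 50, 70 and 85% are shown below.

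**2. Inputs to the simulation.**

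- From the protocol: 1000 × 0.9 = 900 children at end line; 5% level; effect 0.3 SD. A smaller effect of 0.3 HAZ points is also shown: 0.3 / 1.56 = 0.19 SD.
- Assumed: consumer share; lognormal intake among consumers with CV 0.5; A = intake × concentration (log-SD 0.8); β_A = 0; no other covariates; 1500 replicates. The Monte Carlo standard error is at most √(0.25/1500) = 1.3 points, so figures can move by a few points between runs.

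**3. Power of the consumer-only test of β_M.**

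| True benefit | 50% consumers | 70% | 85% |
|---|---|---|---|
| Linear, 0.3 SD at mean intake | 82% | 92% | 97% |
| Linear, 0.19 SD at mean intake | 47% | 58% | 66% |
| Any milk versus none, 0.3 SD | about 5% | about 5% | about 5% |

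With wider intake variation (CV 0.8), the 47% becomes 76%. A separate simulation with gamma intake gave the same pattern for any milk versus none. At 30, 50, 70 and 90% consumers, the consumer-only joint test rejected in 5.5, 4.9, 5.6 and 5.0% of runs, and equation (1) in all children in 95, 96, 86 and 30%.

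**4. What adding the non-drinkers does.** Let D = 1 for drinkers, and M = A = 0 for non-drinkers:

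Y = α + γD + β_M M + β_A A + …

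Non-drinkers then determine α alone, and drinkers have their own intercept α + γ. Without other covariates, the least-squares slopes for drinkers are therefore those of the consumer-only fit; in simulation the two β_M estimates differ by about 4 × 10⁻¹⁵. Testing only (β_M, β_A) in this fit gains nothing: at 50% consumers and 0.19 SD, power is 47% for β_M and 44% for the 2-df test, as among consumers alone. The milk-versus-none information sits in γ, so γ has to be tested too:

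| 3-df test of γ, β_M, β_A | 50% | 70% | 85% |
|---|---|---|---|
| Linear, 0.19 SD | 86% | 87% | 82% |
| Any versus none, 0.3 SD | 98% | 94% | 78% |

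An all-child fit without the indicator also has more power for the linear 0.19 SD benefit (β_M: 77, 83 and 82%), but it forces one slope through both contrasts.

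**The case against.** The restriction stands in the sentence that introduces equation (2), not in the formula, and nowhere does the text say that non-drinkers are dropped. Equation (2) is described as equation (1) with terms added. Milk samples are planned from every household (2000 over two rounds), so C exists for non-drinkers, and A would be zero for them. An all-child fit is thus feasible as written. Nor is a consumer defined as a child with non-zero 24-hour recall: a habitual drinker can have a zero day. M is a continuous amount, and taking both coefficients from one model in one population is coherent.

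Much of this stands. The consumer-only reading is the natural one because it matches the second objective, but it is a reading. If all children are meant, the text should say so and state how A and C are set for non-drinkers.

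Two stronger inferences are tempting and not supported. First, a reader might infer that the plan tilts the comparison against milk. The simulations set β_A to zero, and a joint null of two zeros has no direction; they show lost sensitivity, not bias. Second, a reader might infer that the consumer-only β_M says nothing about benefit. Under linearity it is unbiased and, at the protocol's own 0.3 SD, has at least 80% power in the set-up above. The 5% result needs a benefit with no gradient among drinkers, which the protocol does not posit.

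**Conclusion.** The point holds in a limited form. As the article reads, the benefit term for the third objective reflects only the amount drunk among consumers, and the contrast with children who drink none plays no part in the comparison. The cost runs from a modest loss of precision (linear benefit of 0.3 SD) to no power beyond the 5% level (benefit only from any milk versus none). Where the truth lies between these cannot be told from the document, and every power figure rests on an assumed consumer share and intake distribution. The plan as read relies on extrapolating the consumers' slope down to zero intake, which its own data could check. The analyses for the first and second objectives are not affected. This is a worthwhile, inexpensive improvement.

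**What to change.** 1. State the population for the third objective: equation (2) fitted to all children with end-line data.
2. Set AFM1 exposure to 0 for non-drinkers, add an any-milk indicator (coefficient γ) with a stated definition of a drinker, and enter the milk-content terms for drinkers only.
3. Test γ, β_M and β_A jointly (3 df). A test of β_M and β_A alone in this fit would reproduce the consumer-only result.
4. Report the net HAZ difference from no milk, γ + β_M × intake + β_A × exposure, with its confidence interval at stated intake and AFM1 levels. The joint test alone does not say whether benefit or risk is larger.
5. Keep the consumer-only fit for the second objective.

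This costs analysis wording and code; no further children, samples or visits are needed. The downside is that drinkers and non-drinkers may differ in ways the covariates miss. Equation (1) already accepts that contrast, and reporting the amount slope among drinkers beside the net difference lets readers judge it.

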### Explanatory variables

Child’s milk consumption and AFM_1_ levels in milk are the key explanatory variables in this study. Child’s milk consumption will be measured through a 1-day quantitative multiple-pass 24-hour recall interview, consisting of four steps designed to enhance respondent’s recall accuracy.^24^ We will ensure that all days of the week are proportionately represented during the dietary recall, to account for day-of-the-week effects on food intake. We will also collect a second, non-consecutive day 24 hours recall (repeat), within 2–10 days of the first recall, from a randomly selected subsample of children to account for the day-to-day variability of dietary intake within individuals and for nutrients estimation.

At the baseline and the end-line visits, we will collect milk samples (2000 samples in two rounds). AFM_1_ testing in milk, analysis of dilution of milk, nutrients composition and pathogens testing (including *Escherichia coli and Campylobacter* spp) will be conducted at Ethiopian Public Health Institute (EPHI) laboratory following standard operating practices for handling, processing and storing samples.

AFM_1_ in milk samples will be detected by using a commercial ELISA kit (catering to catalogue no. 961AFLM01C-ULTRA), manufactured by Helica Biosystems of Santa Ana, California, USA.^25^ The methodology for conducting the test will be based on the manufacturer’s guidelines. Standards and samples of 200 µl will be replicated in precoated plates. The resulting mixture will be incubated for 2 hours, followed by washing and the addition of conjugates. After the completion of 15 min of additional incubation and subsequent washing, enzyme substrate of 100 µl will be added to each well, permitted to incubate for 15 min and afterwards stopped using 100 µl of stop reaction. Finally, optical density measurements will be taken at 450 nm for each microwell using a microplate reader. Calculation of AFM1 levels achieved by means of a logarithmic standard curve will require an R^2^ value of no less than 95%. The average results from duplicate readings will be used for the presentation of results.^25^

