## Discussion

The results of this study will inform researchers and policymakers on the impact of AFM_1_ in milk on children’s nutrition outcomes and will have implications for the transforming dairy value chains in Ethiopia. Ethiopia has recently adopted strict AFM_1_ standards in milk and other dairy products, which has led to dairy farmers dumping their milk instead of selling it in the market.^12^ An earlier study showed that cancer risk from AFM_1_ consumption was expected to be extremely low.^12^ However, if AFM_1_ has other harmful health effects, such as compromising child growth, then the strict regulations could be justified. In this study, we can determine whether AFM_1_ levels are higher when animals are fed particular feedstuffs, which—if AFM_1_ is correlated with poorer child growth outcomes—will help identify which crops should not be included in dairy feed. But if our work finds that AFM_1_, independently of livestock feed, causes poor child growth outcomes, then the focus need not just be on reducing AFB1 in dairy feed, but also on technologies that can remove AFM_1_ from milk before it is given to children or further processed for other dairy products.

Our work will contribute to rational policymaking and risk communication at local and national levels on whether AFM_1_ poses a risk to children’s health. It will help policymakers and risk communicators in crafting messages balancing the benefits, risks and health outcomes associated with dairy consumption. Secondarily, there could be economic benefits to dairy producers if AFM_1_ is found to have minimal (or no) adverse child growth outcomes, so that standards and regulations can be set at levels appropriate to the true risk, and so that dairy products do not need to be discarded because of overly stringent regulations.^4 39^

There are some limitations of our study. Since a randomised control trial in this context is not feasible, we use a quasi-experimental approach to understand the risks and benefits of child milk consumption in this context and aim to minimise the risk of bias by controlling for observable confounding factors. We use the 24-hour dietary recall and the limitation of this method is that it only captures food intake in the 24 hours prior to the interview. To address this, we will collect data on the consumption of food groups in the past 7 days and also ask whether the milk quantity consumed in the last 24 hours reflects the typical quantity consumed by the child.

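### The benefit-risk objective is tested with a null that both coefficients are zero, which cannot show whether the benefit of milk exceeds the AFM1 risk or at what AFM1 level

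*Protocol article*

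**What the plan says.** The third objective (Objectives) reads: "Compare the health benefits and risks associated with dairy consumption in relation to child growth outcomes". In Data analysis, Empirical approach, the estimates from equation (2) are to serve this comparison through a joint hypothesis test on beta_M (milk intake) and beta_A (AFM1 exposure), "where the null hypothesis is that both of these coefficients are zero, to inform benefit-risk tradeoff of dairy consumption".

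The same section expects beta_M to be positive and beta_A to be negative. For the second objective it asks separately whether consumption of contaminated milk "is associated with lower HAZ (ie, more growth faltering) controlling for confounders and co-factors, including the amount of milk consumed".

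The article names no net effect, no linear combination of the two coefficients, and no intake or AFM1 concentration at which to weigh them.

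**The concern.** A trade-off question asks which of two opposing effects is larger, and at what level of contamination. A test that both are zero asks whether there is any association at all. It can reject because of benefit alone, harm alone, or both together, including the case where they cancel. Taken as written, the study could report a clear result for its third objective without having compared anything.

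This matters because the Discussion hopes for findings "so that standards and regulations can be set at levels appropriate to the true risk", and the Introduction gives the limits in question: 0.5 µg/L in Ethiopia and the USA, and 0.05 µg/L in the European Union. The joint test bears on neither limit.

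**Working it through.** **The plan's own figure.** The article gives no power or size for the benefit-risk test. Its only design figure is the sample size: "With the significance level set at 5%, power at 80%, allowing for 10% attrition between survey rounds", and "the study requires approximately 1000 children to detect a 0.3 SD improvement in child HAZ". With two equal groups, a two-sided test and 0.3 SD, this gives 175 per group, 350 in total, and 350/0.90 = 389 after attrition. Reading the effect as 0.3 HAZ units with SD 1.56 gives 425 per group, 850 in total, and 850/0.90 = 945. The share of milk consumers enters the calculation but is not stated, so 1000 can be neither confirmed nor called wrong. The point below does not depend on it.

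**Direction.** Write b = (beta_M, beta_A) and V for the covariance matrix of the estimates. The joint Wald statistic is W = b' V^-1 b. Since (-b)' V^-1 (-b) = b' V^-1 b, every pair of coefficients with a net benefit has a counterpart with a net harm of the same size and the same chance of rejection. This is algebra and needs no assumption.

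**AFM1 has no effect.** Set beta_A = 0 and give the single two-sided 5% test of beta_M 80% power.
- Noncentrality of the single test: (1.960 + 0.842)^2 = 7.849.
- Joint test: 2 degrees of freedom, critical value 5.991, noncentrality 7.849/(1 - r^2), where r is the correlation of the two estimates.
- Rejection probability: 0.709 at r = 0, 0.752 at r = 0.3, and 0.834 at r = 0.5.

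**Both effects present.** Assumed for illustration: 900 children analysed (1000 x 0.90), about 30 model parameters, exposures and residual scaled to SD 1, and exposure correlation rho. The noncentrality is 900 x (beta_M^2 + 2 rho beta_M beta_A + beta_A^2). The signed contrast beta_M + beta_A has standard error sqrt(2/(900(1 + rho))), which is 0.047 at rho = 0 and 0.038 at rho = 0.5.

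| Truth (beta_M, beta_A) | Noncentrality, rho = 0 | Joint test rejects, rho = 0 | Joint test rejects, rho = 0.5 | Contrast shows benefit / harm, rho = 0 |
|---|---|---|---|---|
| Benefit larger (+0.15, -0.05) | 22.5 | 99.3% | 95.3% | 56.4% / 0.0% |
| Risk larger (+0.05, -0.15) | 22.5 | 99.3% | 95.3% | 0.0% / 56.4% |
| Exactly balanced (+0.10, -0.10) | 18.0 | 97.4% | 76.9% | 2.5% / 2.5% |
| Milk effect only (+0.15, 0) | 20.25 | 98.6% | 98.6% | 88.9% / 0.0% |
| AFM1 effect only (0, -0.15) | 20.25 | 98.6% | 98.6% | 0.0% / 88.9% |

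At rho = 0.7 the balanced case has noncentrality 900 x (0.02 - 0.014) = 5.4 and rejects in 53.5%. At rho = 0.5 the contrast finds the true direction in 73.8% of studies in each of the first two rows. Those two rows match exactly because both exposures are on the same scale.

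The joint test does not separate the rows. The signed contrast does, at lower power.

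**The case against.** The strongest reply is that the joint test is not used alone. The article says the estimates of equation (2) will be used and that the test informs the trade-off. It sets no decision rule. Signed estimates of both coefficients are planned outputs, and the AFM1 coefficient is tested on its own for the second objective. A joint test is also a valid screen for any association, and rejecting when its null is false is correct behaviour.

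Much of this stands, and it limits the point. Still, two coefficients in different units, read side by side, are not a comparison. Weighing them needs a stated intake and concentration, and an interval that uses their covariance. Nor is this a detail left to an analysis plan, because the article itself fixes the null.

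Four stronger readings may tempt a reader, and the article does not support them.
- **That all the policy conclusions rest on the joint test.** The regulatory reasoning in the Discussion turns on whether AFM1 harms growth, which is the second objective.
- **That non-rejection would be taken as safety.** The Discussion speaks of AFM1 being found to do minimal or no harm. It does not mention the joint test or equate non-significance with absence of harm.
- **That the article confuses concentration with exposure.** Explanatory variables says that milk consumption and AFM1 "levels in milk are the key explanatory variables in this study". These are the measured ingredients of an exposure. The wording about levels in Empirical approach belongs to a separate analysis against nutrient density. How the exposure variable is built may be left to the full plan.
- **That no trade-off can be formed if the AFM1 variable is a concentration.** It can, once an intake and a concentration are both set.

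**Conclusion.** The point holds for the third objective and should be fixed. The named test cannot say whether benefit exceeds risk, in which direction the balance lies, or how it changes with AFM1 concentration.

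The lack of direction is algebraic. The sizes are illustrative. The 71% to 83% assumes 80% power for the milk coefficient and a correlation of 0 to 0.5 between the estimates. The 53.5% to 97.4% assumes standardised effects of +0.10 and -0.10 in 900 children, with exposure correlation from 0.7 to 0.

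The primary outcome, the data collection and the first two objectives are unaffected. As the article itself says that the design does not allow causal inference, the quantity to report is a net association.

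**What to change.** Make the signed net association from equation (2), with a 95% confidence interval that uses the covariance of the two estimates, the main quantity for the third objective. Give it at stated milk intakes m and AFM1 concentrations c, for example 0.05 and 0.5 µg/L and the observed quartiles.

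- **If the AFM1 variable is intake x concentration:** m(beta_M + beta_A c), with variance m^2[Var(beta_M) + c^2 Var(beta_A) + 2c Cov(beta_M, beta_A)].
- **If it is a concentration:** beta_M m + beta_A c, with variance m^2 Var(beta_M) + c^2 Var(beta_A) + 2mc Cov(beta_M, beta_A), or a model with an intake-by-concentration interaction.
- **Controls:** Control variables lists calories from dairy products among the diet controls. Leave that term out of the model for this contrast. Otherwise beta_M compares children with equal dairy calories and loses part of the benefit of milk. State also that the contrast holds at fixed milk nutrient content, because equation (2) conditions on it.
- **Break-even concentration:** report it only as a secondary result (-beta_M/beta_A when the variable is a dose), with a Fieller or bootstrap interval. Say that the interval may be unbounded when beta_A is near zero.
- **Joint test:** keep it as a preliminary screen only.

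The cost is a change of wording and a few lines of Stata, with no new data. The drawback is that the net-association intervals may be wide.

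### The benefit-risk objective is tested with a joint null that both coefficients are zero, which cannot show whether AFM1 partly offsets, cancels or outweighs the benefit of milk

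*Protocol article*

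**What the plan says.** The Objectives section of the protocol article lists as its third aim: "Compare the health benefits and risks associated with dairy consumption in relation to child growth outcomes".

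The Empirical approach section gives this aim one analysis. Equation (2) regresses the growth outcome on milk intake (beta_M), AFM1 exposure (beta_A), milk nutrients and pathogens, maize consumption and the general controls. A joint test of beta_M and beta_A follows, "where the null hypothesis is that both of these coefficients are zero, to inform benefit-risk tradeoff of dairy consumption".

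Two other statements in that section bear on the point:
- After equation (1), a positive beta_M is anticipated: "Considering previous evidence from Ethiopia and elsewhere, we expect" introduces that sign.
- For Objective 2 the AFM1 coefficient is examined separately: "we will test whether the consumption of AFM_1_-contaminated milk is associated with lower HAZ". A negative beta_A is expected.

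The article gives no net effect, signed contrast, ratio or break-even level. It also does not say whether the AFM1 variable A_iv is a concentration or a dose (intake times concentration).

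**The concern.** A comparison of benefit with risk asks which is larger, and at what level of contamination. The stated null is false as soon as either coefficient differs from zero, so a benefit of milk alone is enough to reject it. The F or Wald statistic has no sign, so rejection fits harmless AFM1, partial offset, exact cancellation and net harm equally. Failure to reject would not show balance either, because exact cancellation also violates the null.

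The Discussion says the results will inform AFM1 standards and messages that weigh dairy's benefits against its risks. A significant joint test could be presented as evidence on that trade-off although it does not address which effect is larger.

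**Working it through.** **The plan's own figure.** No figure is given for the joint test. The only design figure is about 1000 children.
- 0.3 SD, two-sided 5%, 80% power: 2 × (1.96 + 0.84)² / 0.3² gives 175 per group, 350 in all. With 10% attrition, 350 / 0.9 = 389.
- Read as 0.3 HAZ units with SD 1.56: 425 per group, 850 in all, and 850 / 0.9 = 945.

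The article says it is "accounting for that not all children consume milk" but does not give the share, so 1000 can be neither confirmed nor refuted. The point does not depend on it.

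**Inputs for the joint test**
- n = 900: 1000 less 10%, from "allowing for 10% attrition between survey rounds" in Sample size calculations.
- Two-sided 5% (the article gives 5% without sidedness).
- Assumed: beta_M = 0.15 outcome SD per SD of milk intake. This corresponds to 0.3 SD between two equal groups, since a 50:50 indicator has SD 0.5 and 0.3 × 0.5 = 0.15.
- Assumed: residual SD 1, 20 model parameters, exposure correlation r of 0, 0.3 or 0.6. None of these is in the article.

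**Formula.** 2-df noncentral F with noncentrality n × (beta_M² + beta_A² + 2r × beta_M × beta_A). With beta_M = 0.15 and n = 900:
- AFM1 harmless (beta_A = 0): 900 × 0.0225 = 20.25 at any r.
- AFM1 cancels (beta_A = −0.15): 900 × 0.0225 × (2 − 2r) = 40.5, 28.35 and 16.2 at r = 0, 0.3 and 0.6.
- AFM1 outweighs by half (beta_A = −0.225): 900 × 0.0225 × (3.25 − 3r) = 65.8, 47.6 and 29.4.

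| Situation | Net (beta_M + beta_A) | r = 0 | r = 0.3 | r = 0.6 |
|---|---|---|---|---|
| Harmless | +0.15 | 0.986 | 0.986 | 0.986 |
| Cancels | 0 | 1.000 | 0.999 | 0.958 |
| Outweighs | −0.075 | 1.000 | 1.000 | 0.999 |

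The last three columns are rejection probabilities. Using 25 parameters instead of 20 leaves the r = 0.6 results for the harmless and cancelling cases unchanged (0.986 and 0.958). A simulation with exposure equal to intake times concentration, and cancellation set at the mean concentration, gave 0.986, 1.000 and 1.000.

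**Smaller samples.** With n = 700 the range over the same cells is 0.897 to 1.000. With n = 389 and r = 0.6 the three cases give 0.76, 0.65 and 0.90: the decisions are less uniform, but they still do not put the cases in order.

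**The alternative, on the same assumptions.** For the signed contrast beta_M + beta_A, the standard error is √(2 / (n(1 + r))). At n = 900 and r = 0.3 this is √(2 / 1170) = 0.041.
- Harmless: significantly positive with probability 0.95.
- Cancels: 0.025 in each direction.
- Outweighs: significantly negative with probability 0.44.

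The contrast separates the three cases, although its power for a small net harm is low.

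**The case against.** The strongest reply is that the joint test does not stand alone. Equation (2) will yield signed estimates of both coefficients, and Objective 2 tests beta_A on its own. A reader might infer from the joint null that the study has no estimate bearing on the trade-off, or cannot see AFM1 harm at all. The documents do not support that: harmless and harmful AFM1 can be told apart. What remains is narrower. Two coefficients on different exposure scales do not give a net association or its interval; that needs a stated intake, a stated AFM1 level and the covariance of the estimates.

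A reader might also infer that the joint test is weakest where the trade-off is real, because the two effects offset. For equal and opposite slopes the noncentrality is below that of the harmless case only if 2 − 2r < 1, that is, if r exceeds 0.5. At r = 0.3 and n = 900 cancellation is rejected more often (0.999 against 0.986). The article gives no exposure correlation, so this cannot be stated in general.

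Nor does the article say outright that it expects its own joint null to be false. The positive sign is stated for beta_M in equation (1); the joint test uses beta_M from equation (2), which also adjusts for milk nutrients and pathogens. Carrying the expectation over is a plausible inference, but only that.

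Finally, it may be said that such detail belongs in a statistical analysis plan. That would answer an omission. Here the article names the null itself, and a plan that followed it would carry the same hypothesis forward.

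**Conclusion.** The concern holds in this form: the hypothesis fixed for Objective 3 does not compare benefit with risk, and no stated analysis separates partial offset, cancellation and net harm. This follows from the form of the null and needs no assumption. The size does rest on assumptions: with slopes of 0.15, n = 900 and an exposure correlation of 0 to 0.6, all three situations are rejected with probability of about 0.96 to 1.00. The same decision in every case therefore presupposes adequate power.

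This should be fixed, but it does not threaten the study as a whole. Sampling, measurement, the primary outcome and the regression model are untouched, and the change can be made before analysis.

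**What to change.** In the Empirical approach section, replace the joint null as the benefit-risk analysis with an estimate:

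1. **State the unit of A_iv.** If it is intake times concentration, the net association at intake m and concentration c is m × (beta_M + c × beta_A). If it is concentration, it is m × beta_M + c × beta_A. Without the unit the combination is undefined.
2. **Report the net association with its 95% confidence interval**, using the covariance of the two estimates, at a stated milk intake and stated AFM1 levels. Candidates are the 0.05 and 0.5 µg/L limits cited in the Introduction and a high percentile of the sample.
3. **Say what it is conditional on.** In equation (2) beta_M is adjusted for milk nutrients, and the planned diet controls include calories from dairy. A net figure from that model may understate the benefit of milk. Label it as conditional, or also report it from a model without the controls that carry milk's own benefit.
4. **Optional:** add the AFM1 level at which the net association is zero, noting that its interval can be unbounded when beta_A is near zero. The joint F-test can stay as a descriptive line.

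The cost is about a paragraph of text and one post-estimation command on a model already planned; item 3 may add one further regression. The downside is that the interval may be wide and look less favourable than a significant joint test.
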